**Clinical Trial Schedule**

| Items | Treatment and Observation Period | | | | | |
| --- | --- | --- | --- | --- | --- | --- |
| No. of Visits | Visit 1 | Visit 2^1)^ | | Visit 3 | Visit 4 | Visit 5 |
|  | Before surgery | Immediately after surgery | 7 days after surgery | 3 month after surgery | 6 months after surgery | 12 months after surgery |
| Visit Window (Day) |  |  | ± 2 | ± 14 | ± 14 | ± 30 |
| Inclusion/ Exclusion Criteria | ○ |  |  |  |  |  |
| Informed Consent | ○ |  |  |  |  |  |
| Basic Information and Medical History | ○ |  |  |  |  |  |
| Hematologic Tests^2)^ | ○ |  | ○ |  |  |  |
| Measurement of drainage volume^3)^ |  | ○ | ○ |  |  |  |
| Analysis of body composition | ○ |  |  | ○ | ○ | ○ |
| Investigational medical device prescription |  | ○ |  |  |  |  |
| Measurement in the range of shoulder joint’s motion | ○ |  |  | ○ | ○ | ○ |
| Evaluation on the upper limbs’ locomotive capacity | ○ |  |  | ○ | ○ | ○ |
| Evaluation of pain | ○ |  |  | ○ | ○ | ○ |
| Evaluation of Adverse Events |  |  | ○ | ○ | ○ | ○ |

1) The test for blood and the adverse events scheduled on the visit 2 will be evaluated based on the adverse events discovered on the discharge date of patient or on the 7th day subsequent to the surgery by revisiting the patient.

2) Hematologic Tests - WBC, Neutrophil

The blood test to be performed on the 7th day subsequent to surgery will be conducted only if the adverse events such as the flare onto the surgical site or the fever exists following the surgery. The intention of above-mentioned test (test item: CBC, CRP, and etc.) is to check whether the inflammation factor is increased and the number of white blood cell within 7 days from the surgery.

3) Measurement of drainage volume - Shall be measured at an interval of two days until the 7th day from the surgery date and complete the measurement of it on the discharge date from hospital.

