**11. Monitoring Items and Monitoring Methods**

**11-1 Monitoring Items and Methods**

(1) Information Consent and Demographical Data

Before participating in the clinical trial, the purpose and procedure of clinical trial are explained to subject in detail and demographical information such as the receipt of the written consent and date, subjects’ initials, height, and BMI is recorded in the CRF. The copy of informed consent form is provided to the subject after receiving the written consent from subject.

(2) Past History and Physical function

The subject will be informed about the clinical trial continually. We recorded the stage of disease, medical history, the info related to the predisposing conditions on the shoulder joint, blood test, the range of shoulder joint’s motion, the evaluation on the exercise capability of upper limbs, and the evaluation on pain derived from the movement.

(3) Subject Eligibility Evaluation (Inclusion/Exclusion Criteria checking)

recorded the result conducted after evaluating whether the suitable subject is selected according to the inclusion/exclusion criteria based on the consent for the participation of clinical trial, demographical survey, medical history, the preoperative histological diagnosis, and etc.

(4) Observation items related to the surgery

- Basic information on the surgery

Operation date, Name of surgery, histopathological diagnosis, TNM stage, postoperative therapy (cancer chemotherapy, anti-hormone therapy, target therapy, radiotherapy)

- Safety evaluation

Adverse events (complication discovered during the hospitalization and surgery-related complication), Measurement of drainage volume subsequent to surgery, Observation of infectious symptom, Complete blood count exam (POD#7)

(5) Physical function (Before surgery, after surgery 3, 6, 12 months)

- Efficacy evaluation

Shoulder range of motion (Abduction, Horizontal abduction, Flexion, External rotation), Evaluation on the upper limbs’ locomotive capacity, the evaluation on pain derived from the movement, Evaluation on the lymphedema using the analysis of body composition

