**11-3 Assessment of Safety Criteria and method**

(1) Laboratory Tests

Hematologic Tests – WBC, Neutrophil

(2) Evaluation of Adverse Events

Investigators shall educate the subject to report the adverse events voluntarily and occasionally and check the adverse events which occurs in the subject by interviewing or reviewing the report kept in hospital during the visit.

(3) The evaluation on pain derived from the movement

(4) Drainage volume subsequent to the surgery

Drainage volume (ml) unit shall be surveyed.

(5) Expected Adverse Events

In case of the infection which occurs as an adverse events following the use of investigational medical device, we confirmed its degree by checking up the clinical sign and performing the blood test (the white blood cell count (WBC)) scheduled to 7th following the surgery.
In case of the allergic reactions (generalized eruption, respiratory dyspnea, edema, pain, and inflammation), we analyzed the causal relationship with the usage of investigational device by checking up the clinical signs.

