 Preoperative histological diagnosis

 Laboratory Tests were conducted

 Physical function (Shoulder range of motion: Abduction, Horizontal abduction, Flexion, External rotation), Evaluation on the upper limbs’ locomotive capacity, the evaluation on pain derived from the movement

 The analysis of body composition

 Evaluation on the subject eligibility for this clinical trial

② Visit 2(OPD~POD #7)

 The investigational device was applied (The EG, The CG Randomization)

 Histopathological diagnosis and TNM stage

 Postoperative adjunctive therapy (cancer chemotherapy, anti-hormone therapy, target therapy, radiotherapy)

 Postoperative total capacity

 Laboratory Tests were conducted (POD #7)

 Evaluation of Adverse Events

③ Visit 3, 4, 5(POD 3, 6, 12 months)

 Physical function (Shoulder range of motion: Abduction, Horizontal abduction, Flexion, External rotation), Evaluation on the upper limbs’ locomotive capacity, the evaluation on pain derived from the movement

 The analysis of body composition

 Evaluation of Adverse Events

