**12-4 Expected adverse events when using the anti-adhesive agent**

Infection: Fever and increase in WBC, Allergic reactions: Systemic rash, dyspnea, and edema, Pain, Inflammation

* Guardix SG (Anti-adhesion) is to prevent the adhesion having a physical barrier in order for the fibroid tissue to infiltrate to the damaged tissue. We recorded the degree of adverse events ranging from mild, moderate, and severe depending on the patient and the state since its degree is diverse regardless of same symptom.

(1) Mild: The degree of adverse events is mild.

(2) Moderate: The degree of adverse events is moderate.

(3) Severe: The degree of adverse events is severe.

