**15-2 Safety Criteria Analysis**

(1) Adverse Events

All the AE that developed during the study period were analyzed. Their onset rate, the onset rate of AE that caused dropout, and the onset rate of SAE were summarized by group. They were coded using WHO-ART, then tested through the Chi-square test or Fisher’s exact test. The onset rates of AE were suggested as: onset rate of all adverse events, and the onset rate associated with the investigational device.

(2) Laboratory Tests

In the case of baseline continuous data from the laboratory test, descriptive statistics quantity (such as mean, SD, median, minimum, and maximum) was calculated, and their normal distribution was tested, then the difference between the groups was compared using One side, Two sample student t-test. In the case of categorical data, their descriptive statistics quantity (frequency and percentage) was suggested, and the difference between the groups was compared using the Chi-square test or Fisher’s exact test. After checking the investigational group’s test value came out on preoperative day and the 7th day following the surgery is different from it of control, we checked whether this difference is included within the normal error range or not.

1) Assessment of Criteria: Adverse events (Visit2, Visit3, Visit4, Visit5) and Hematologic Tests (Visit1, Visit2)

2) Evaluation criteria: The safety of investigational device is considered to be confirmed if the difference between the investigational group’s result value and control’s result value isn’t significant.

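### Day-7 blood counts are taken only in patients with events such as flare or fever, yet the arms' day-7 values are compared and non-significance counts towards confirmed safety

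*Protocol*

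**What the plan says.** **Who is tested.** Footnote 2 of the Clinical Trial Schedule, repeated under the schedule in section 11-4, reads "The blood test to be performed on the 7th day subsequent to surgery will be conducted only if the adverse events" such as flare at the surgical site or fever exist. Section 11-3 (5) is consistent with this: it begins "In case of the infection which occurs as an adverse events following the use of investigational medical device" and then uses clinical signs and the day-7 white-cell count to establish the degree of infection. Two list entries leave the condition out: "Complete blood count exam (POD#7") in 11-1 (4) and "Laboratory Tests were conducted (POD #7") under Visit 2 in 11-4.

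**What is compared.** Section 15-2 (2) asks whether the investigational group's "test value came out on preoperative day and the 7th day following the surgery is different from it of control". The items for assessment are "Adverse events (Visit2, Visit3, Visit4, Visit5) and Hematologic Tests (Visit1, Visit2").

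**How it is judged.** The next line of 15-2 (2) gives the rule: "The safety of investigational device is considered to be confirmed if the difference between the investigational group" and the control group is not significant.

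**What the device may cause.** Section 12-4 lists the expected events of the agent: "Infection: Fever and increase in WBC, Allergic reactions: Systemic rash, dyspnea, and edema, Pain, Inflammation".

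**The concern.** The trigger for the day-7 test arises after randomisation, and section 12-4 says the device may influence it. Among tested patients the comparison is therefore between symptomatic device patients and symptomatic control patients, and randomisation no longer protects it. Suppose the device doubled the infection rate, each infection raised the white-cell count by the same amount, and only infected patients were tested. The expected difference between the tested groups would then be zero, and the rule would usually count that towards confirmed safety.

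The subset may also be small, so a non-significant result is likely whatever the truth. The sampling rule, the comparison and the decision rule are all fixed in the protocol. A later analysis plan cannot recover samples that were never taken.

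**Working it through.** **Inputs from the protocol.** Section 8-3 gives 96 randomised per arm and a one-sided alpha of 0.025. The figure of 96 reproduces: with 5 degrees beyond the margin, SD 10 and 86 per arm, noncentral-t power is 0.9032, matching the table row, and 86/0.90 = 95.6, rounded up to 96. That calculation concerns range of motion. The protocol gives no figure for the day-7 blood comparison.

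**Assumptions.** The protocol states no trigger rate, infection rate or white-cell effect, so ranges are used. Section 15-2 (2) attaches its t-test to baseline data and names no separate day-7 test. A two-sample t comparison is assumed here because criterion 2) speaks of significance.

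**Step 1: precision in the tested subset.** Assume equal trigger rates in both arms, the same SD in tested patients as in all, and a uniform shift of 0.5 SD. The half-width of the 95% CI is t(0.975, 2n-2) × √(2/n). Power comes from the noncentral t distribution.

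| Share tested | n per arm | Half-width (SD) | Power for 0.5 SD | Missed |
|---|---|---|---|---|
| 5% | 5 | 1.46 | 0.104 | 90% |
| 10% | 10 | 0.94 | 0.184 | 82% |
| 20% | 19 | 0.66 | 0.323 | 68% |
| 30% | 29 | 0.53 | 0.465 | 53.5% |
| 100% | 96 | 0.28 | 0.931 | 7% |

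**Step 2: bias from selection.** Assume infection in 5% of control and 10% of device patients, a 2 SD rise in white cells with infection, and all infected patients tested. Let p be the infection rate and s the rate of flare or fever in uninfected patients. The infected fraction among those tested is p / (p + (1-p)s). The expected difference is 2 SD times the difference between the arms' fractions. The true difference over all patients is (0.10 - 0.05) × 2 = +0.10 SD.

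| s, control v device | Infected fraction, control v device | Selected difference (SD) |
|---|---|---|
| 0 v 0 | 1.000 v 1.000 | 0.00 |
| 0.05 v 0.05 | 0.513 v 0.690 | +0.35 |
| 0.15 v 0.15 | 0.260 v 0.426 | +0.33 |
| 0.05 v 0.15 | 0.513 v 0.426 | -0.17 |

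With s above zero, the selected difference is zero when the ratio of s (device to control) equals the infection odds ratio: (0.10/0.90)/(0.05/0.95) = 2.11, for example 0.05 v 0.106. This point does not depend on the size of the white-cell effect. Below it the selected difference is positive, and above it negative.

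**Step 3: simulation of the case where every tested patient is shifted equally.** With 96 per arm, SD 2 units and a rise of 5 units in patients with an event, 4,000 runs per setting give:

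| Event rate, control v device | Significant, tested patients only | Significant, everyone tested |
|---|---|---|
| 5% v 20% | about 2% | about 52% |
| 10% v 30% | about 3% | about 70% |

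The subset comparison stays near its nominal 2.5% despite a real excess of events on the device.

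**The case against.** **The precision contrast depends on a uniform shift.** This stands. In the infection scenario of Step 2, simulation (96 per arm, one-sided 0.025, 8,000 runs per setting) shows that testing everyone detects harm in only about 8-9% of trials. Testing triggered patients alone detects it in about 9% (s = 0.05 in both arms) or 11% (s = 0.15 in both), so selection costs no power there. It loses with no non-infectious triggers (2% v 9%) or with three times as many on the device (1% v 9%). The miss rates of 53.5-90% against 7% should not be carried over to that mechanism.

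**The direction may be conservative.** With equal, non-zero trigger rates the subset overstates harm. This also stands, but it shows that the comparison does not estimate the right quantity. It does not make the comparison valid.

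**No day-7 test is named.** The day-7 sentence can be read as a check against a normal range. However, Visit 2 hematology is listed under a significance rule, and the selection problem is the same whichever test is used.

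**Adverse events already catch infections.** Largely true. Sections 14-2, 15-2 (1), 16-1 and 16-2 (1) bring symptoms and abnormal laboratory findings into the adverse-event comparison over all patients. This limits the consequence, but the laboratory values remain a named input to the safety conclusion.

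**Testing only symptomatic patients is clinically sensible.** Agreed; the objection here is to the comparison built on it. The unconditional entries in 11-1 (4) and 11-4 do not override an explicit restriction stated twice.

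**Conclusion.** The concern holds. The protocol samples day-7 blood by a post-randomisation event and then uses a between-arm comparison of those values towards confirming safety. That conclusion follows from the text and needs no assumed rate.

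The size is illustrative, because it rests on trigger rates, infection rates and a white-cell effect that the protocol does not give. Across the ranges shown, precision is roughly two to five times worse than with full testing (0.53/0.28 = 1.9; 1.46/0.28 = 5.2), and the bias may go either way. The primary endpoint and the all-patient adverse-event comparison are not affected. The change should be made, because as written the laboratory part of the safety criterion cannot support the conclusion drawn from it.

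**What to change.** 1. In 11-1 (4) and in the Visit 2 list of 11-4, add the condition to the day-7 test: *only if an adverse event such as flare at the surgical site or fever occurs*. Section 11-3 (5) can stay.

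2. In 15-2 (2), replace the day-7 comparison with:

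> Day-7 WBC and neutrophil values are listed descriptively for tested subjects and are not compared between groups. By group, over all randomised subjects, the number with a triggered day-7 test and the number with a triggered test showing an abnormal result are given with the risk difference and 95% CI. These are symptomatic abnormalities only; untested subjects are not taken as normal.

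3. Take Visit 2 hematology values out of criteria 1) and 2) of 15-2 (2). Visit 1 hematology stays as a baseline description. The adverse-event comparison in 15-2 (1) and the abnormal laboratory findings in 14-2 stay as they are.

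The cost is wording in three sections and one small table that partly overlaps the adverse-event tables, with no extra blood tests. Testing every patient on day 7 would also remove the selection, but at the price of a draw in all patients, and non-significance would still be read as safety.

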**1. Title of Clinical Trial**

Title of Clinical Trial

: The application efficacy of (Guardix SG), a mixed liquid (Poloxamer and Alginate) in the range of motion of patient’s shoulder joint scheduled to undergo the modified radical mastectomy or the breast preservation surgery and the axillary lymph node dissection: A randomized, single center, prospective, inactive control, superiority, subject and assessor-blinded, and the investigator-initiated clinical trial.

**6. Purpose and Background**

**6-1. Purpose**

We want to know about the application efficacy of (Guardix SG), a mixed liquid (Poloxamer and Alginate) in the range of motion of patient’s shoulder joint scheduled to undergo the modified radical mastectomy or the breast preservation surgery and the axillary lymph node dissection

**6-2. Background**

The various adverse events on the upper limbs such as the pain on the arm, the muscle weakness, the lymphedema, hypofunction of shoulder joint, and etc. occur following the breast cancer surgery. The shrinkage in the range of shoulder joint’s motion and the muscle weakness lead to the reduction in activities’ scope of daily living and the decline the quality of life [2-6]. Therefore, the treatment and effort to prevent the complication which occurs especially when the axillary lymph node dissection is performed is needed. Koostra et al. reported the complication (such as lymphedema, the range of shoulder joint’s motion, muscular strength, the exercise of upper limbs, and etc.) occurrence rate of patients who underwent the surgery on the sentinel node is lower than it of patients who underwent the axillary lymph node dissection in terms of statistical significance found at prospective studies. The significant factor related to the reduction in the range of shoulder joint’s motion affects the treatment method and the recovery period [1].

The occurrence rate of pectoralis tightness and the reducing degree in the range of shoulder joint’s motion of patients who underwent the mastectomy are higher than those of patients who underwent the breast preservation surgery. The quality of radiotherapy subsequent to the surgery also affects the occurrence rate of above-mentioned complications. The reducing degree on the range of shoulder joint’s motion is the largest within 12 months subsequent to the surgery and its reducing degree is small since that time [3-6].

Since the adhesion of surgical site which can occurs after the total mastectomy causes the reduction in the range of shoulder joint’s motion and the pain, the measure for reducing the above-mentioned symptoms significantly is needed by developing the method to prevent the adhesion. The fact that the application of HA-CMC onto the surface of pectoral muscle and serratus anterior muscle, the treatment for preventing the adhesion followed by the surgery, widened the range of shoulder joint’s motion of breast cancer patients and reduce their pain is discovered in the previous study on HA-CMC [17]. In addition, the other studies on HA-CMC showed the range of joint’s motion is widened after the application of HA-CMC which lessened the adhesion degree [21].

Methods of preventing adhesion may include the minimization of surgical wounds, use of anti-inflammatory agents, and activation of tissue plasminogen activators for inhibiting fibrin formation [18]. Recently physical barriers have also been developed and used [19]. Barriers function as a physical barrier during the tissue healing period and prevent adhesion formation around the tissues. Upon completion of wound healing, the barrier must be dissolved or absorbed to be removed. The barrier itself and its dissolved ingredients must be harmless to the body. Adhesion prevention materials may include oxidized regenerated cellulose, sodium carboxymethyl cellulose (CMC), dextran, and sodium hyaluronate (HA), which are made from nature-derived polysaccharides. Synthetic polymers may include polyethylene glycol (PEG), poloxamer, and Gore-Tex.

The anti-adhesive agent, which builds the physical barrier, is made from the various materials and its type is various. The double liquid type has a convenient usage of which solution is applied underneath the wound directly and used well since it can be used in the laparoscopic surgery. However, it has a weakness of which efficacy is reduced when its liquid solution flows.

GUARDIX SG is prepared using poloxamer, a synthetic macromolecule, and alginate, a natural macromolecule. It is liquid at room temperature, but when applied to surgical sites, it reacts to the body temperature to function as a gel. As a temperature-sensitive adhesion barrier, it remains in the body for up to 7 days according to in vivo experiments, then begins to dissolve after the 14th day and then is completely dissolved by the 21st day [20].

Guardix SG is the efficacy of anti-adhesive agent is already confirmed at the rat and the anti-adhesive efficacy and safety of it is confirmed clinically by using it for the patient who underwent spondylectomy and the thyroidectomy [18-20, 22].

Based on the above-mentioned grounds, we intended to evaluate the safety of Guardix SG and the preventive efficacy of Guardix SG for the dysfunction of upper limbs within the breast cancer patients who underwent the modified radical mastectomy or the breast preservation surgery along with the modified axillary lymph node dissection for 12 months by conducting observation study following the surgery.

**7. Purpose of Using the Investigational Device**

**7-1. Purpose of Using the Investigational Device**

Furthermore, we reviewed the preventive efficacy of investigational device for the limitation on the shoulder joint’s postoperative movement by comparing the difference on the range of shoulder joint’s motion between the patients whom Guardix SG is applied onto the surgical site after undergoing the modified radical mastectomy or breast preservation surgery and the axillary lymph node dissection.

**7-2. Indicated Diseases**

Breast cancer

(A patient who underwent the modified radical mastectomy or breast preservation surgery and the axillary lymph node dissection.)

**8. Inclusion/Exclusion Criteria, and Calculation of Subject Number**

**8-1 Inclusion Criteria**

(1) The adult over 20 years old

(2) Patient who is diagnosed as a breast cancer

(3) Breast cancer patient who underwent the modified radical mastectomy or breast preservation surgery and the axillary lymph node dissection(Including the patient who received the preoperative chemotherapy after undergoing the axillary lymph node dissection)

